**Figure 1 figure1:**
[figure not shown]
Selection criteria for mapping and choosing locations for recruitment for the Parcours d’Haïti study between 2021 and 2023. NGO: nongovernmental organization.

At the recruitment sites, random recruitment was carried out—all people meeting the inclusion criteria were invited to take part in the study. Recruitment was halted once we reached a reasonable number of participants from a statistical power perspective and representativity of the study populations.

To improve the representativeness of the sample, additional recruitment using the snowball method was planned among eligible health and social care professionals and resource persons. Each volunteer participant received 8 cards with an alphanumeric code to be distributed to eligible people within their circle. Those who received a card and wished to participate were able to contact the peer investigators to schedule an interview according to their availability. The entire protocol was explained to them, and they were able to ask any questions they wished before agreeing to take part. This method was used to improve the quality of the sample and minimize selection bias in terms of care and social support as well as insecurity.

For the qualitative components, the samples were chosen based on predefined inclusion criteria, developed previously, to represent the different profiles of stakeholders and individuals. Sampling was stopped for each component when data saturation in the answers was reached.

### Study Monitoring

According to the monitoring plan, the compliance of participants’ nonopposition forms (which are equivalent to informed consent forms—the term “nonopposition” is used under French law for studies conducted under Reference Methodology 003) was verified by a clinical research assistant, along with participants’ identity, inclusion criteria, and inclusion group. If reported by the monitoring, participants duplicates or unmatched inclusion criteria led to participants’ exclusion. In addition, where possible, nonopposition forms were completed by the study investigators in conjunction with the clinical research associate. Before data entry, all information collected on the participants’ biographical grid was proofread daily by a peer investigator. In the event of incomplete or inconsistent data, a review was carried out with the investigator who completed the questionnaire. Finally, the data entered were analyzed and checked for logical correctness.

### Data Collection Tools

All the study’s collection tools were coconstructed with health mediators (community health workers) of Haitian origin, the partner structures, the study’s partner physicians (HBV and HIV specialists), the team from the Regional HIV coordination committee (COREVIH) Guyane, researchers from Inserm Clinical Investigation Center 1424, and the study’s scientific partners. The issues of acceptability, confidentiality, and quality were at the center of all discussions. The data from Haitian-born people aged 18 to 60 years included in the quantitative epidemiological section were collected using 2 tools: a cross-sectional epidemiological questionnaire on a tablet (Multimedia Appendix 1) and a paper biographical grid where information was collected year after year (Multimedia Appendix 2). These tools were pretested, and adjustments were made. These questionnaires were both hetero administered, with interviews being conducted in either French or Haitian Creole, and generally took approximately 60 minutes to complete per participant. The interviews took place at the time they were proposed or during an appointment scheduled at the participants’ convenience.

The cross-sectional epidemiological questionnaire collected data related to arrival and stay in French Guiana, history of administrative procedures to stay for medical reasons, sexual and reproductive health, coerced or transactional relationships over the lifetime, use of birth control methods before and after arrival in French Guiana, use of HIV screening tests, general health status, mental health status (4-item Patient Health Questionnaire scale and the psychotrauma scale of the Post-Traumatic Stress Disorder-8), substance use (Alcohol Use Disorders Identification Test–Consumption scale), health insurance coverage, refusal of care experience, food insecurity and hunger, and use of nonallopathic medicine [27-29]. For the groups of participants living with HIV or HBV, 2 short complementary modules were completed in the cross-sectional questionnaire, follow-up and treatment histories were also collected biographically, and medical questionnaires containing routine biological and medical information were completed (Multimedia Appendix 1). Cross-sectional questionnaire data were collected using the ODK Collect software (Get ODK Inc) on tablets. Transversal data entry was conducted offline, and then data were extracted manually using an R script (R Foundation for Statistical Computing) to transform instances into a CSV database [30]. Biographical data were collected on paper biographical grids and then coded using a dictionary of variables and corresponding labels.

The second main tool used was a biographical grid, with the following information collected retrospectively year after year over the lifetime: residential history, administrative history, health coverage, history of professional activities, sources of income, history of relationships, pregnancies and children, history of screening tests for HIV, HBV and cervical cancer screening, history of illnesses and hospitalizations, health or social support structures encountered since arrival in French Guiana, perceived annual well-being, hunger, and significant events. For the groups of participants living with HIV or HBV, follow-up and treatment histories were also collected biographically. The biographical grid data were then entered into Ennov Clinical by a clinical study technician. The decision to freeze the quantitative databases was taken on March 13, 2024, once the data entry and control processes had been completed. The controls continued until June 7, 2024.

Migration routes were also collected on a map and then entered manually into a CSV database (Multimedia Appendix 3).

For the groups of participants living with HIV or HBV, 2 short medical questionnaires containing routine biological and medical characteristics were completed by the physicians in charge of the patients based on their medical history and the results of biological tests.

Finally, a satisfaction questionnaire was administered via telephone at the end of the study to participants who agreed to leave their contact details with the investigators, focusing on the experience and potential benefits derived from taking part in the study and the in-depth personal interview with a mediator (Multimedia Appendix 4). This section was collected by an investigating mediator via telephone using the ODK Collect software. The flow of quantitative, epidemiological, and biographical data, as well as quality control and data verification processes, are detailed in Figure 2.

Qualitative data were collected via semidirective face-to-face interviews, each lasting approximately 45 minutes (Multimedia Appendix 5). With regard to access to health care, the themes addressed were health determinants and access to and use of medical care by migrants in French Guiana. In the case of mental health, we explored the mental health problems of migrants in French Guiana, existing health care services, obstacles encountered, violence experienced, and its link to sexual health. The interviews were in part recorded using a smartphone, anonymized, and fully transcribed.

An ethnographic dimension was also added to the qualitative axis with active observation in Haitian migrants’ neighborhoods. Traditional practitioners were followed in their care the preparation of traditional remedies, as well as in the treatment of patients whenever possible.

**Figure 2 figure2:**
[figure not shown]
Flow of quantitative, epidemiological, and biographical data collected during the Parcours d’Haïti study and quality control and checks on the data.

### Analysis Plan

As the analyses had not yet begun at the time of submission of this work, this section is written in the future tense.

#### Statistical Analysis of Quantitative and Biographical Data

With regard to the statistical analysis of quantitative information, the major indicators will be described using percentages as well as means or medians with their SDs or IQRs depending on their distribution. Analytical work will be carried out with a biographical and social epidemiology approach using the tools of epidemiological analysis to study the associations between behaviors and health indicators and social determinants. Factors associated with biographical key indicators will be analyzed year after year using discrete-time logistic regression models that take into account time and the values of indicators collected in the biographical grid year after year [31]. Factors associated with indicators collected at the time of the study will be analyzed using Poisson regression with robust variance. The Stata software (StataCorp) will be used to conduct the analyses.

An analysis of the participants’ support and care structures will be carried out based on specific questions that will be analyzed through clustering and a bipartite network approach using methods derived from graph theory. These analyses will provide a better understanding of the levers and care itineraries that can be developed. The R software will be used for these analyses (*tidyverse* and *tidygraph* packages).

#### Qualitative Analysis

The qualitative study is of a hypothetical-deductive type conducted following a discursive and recursive approach using semidirective interview grids for individual interviews and in a freer manner for discussion groups. These interviews involve a conversational dynamic in which the interviewer and participants interact in a progressive, recursive, and flexible manner to obtain a broad and comprehensive view of the subject. All interview observations will be triangulated with field observations. The collected data (recorded or handwritten) will be analyzed thematically, manually, or using a specialized software (MAXQDA 2022; VERBI GmbH).

#### Phylogenetic Analysis

For the analysis of Pol gene clades, the data (nucleotide sequences) will be extracted from the HIV resistance genotype by the Pasteur Institute laboratory in French Guiana, an analysis conducted for all people living with HIV before antiretroviral therapy. A phylogenetic tree will be produced from these sequences, and the clades to which they belong will be analyzed. The results of the phylogenetic analyses (clades) will be described in the form of phylogenetic trees and cross-referenced with social and biographical determinants, and associations will be analyzed using chi-square tests conducted using the Stata software. These analyses will be carried out in part by the Oswaldo Cruz Institute of Fiocruz in Rio de Janeiro.

## Results

### Overview

For 20 months, the Parcours d’Haïti study was implemented and conducted in French Guiana. The initial study was enriched and developed, and 3 substantial modifications were made.

In November 2021, the first participant was recruited for the quantitative epidemiological component, which focused on people living with HIV and the general Haitian population. In June 2022, a group of people living with HBV was added to the study. Several approaches were developed using a mixed methodology: a quantitative cross-sectional approach; a quantitative biographical approach; a qualitative mental health approach; a qualitative approach to access and use of care; an anthropological and ethnobotanical component; and, finally, a “satisfaction” component. These elements are shown chronologically in Figure 3.

**Figure 3 figure3:**
[figure not shown]
Chronological timeline of the different axes of the Parcours d’Haïti study between 2020 and 2025.

### Quantitative and Biographical Data

For the quantitative component, recruitment was completed by May 31, 2023. Data quality control has been extended to June 2024. Analysis is scheduled to begin in July 2024. The collection of migratory routes was completed on May 31, 2023. The first results are expected at the end of 2024.

### Qualitative and Anthropological Data

Qualitative data were collected along the 3 axes mentioned previously. The first section on mental health has been completed, and the first results on mental health are expected at the end of 2024. The section on access to and use of health care has been completed, the interviews have been analyzed, and this work was published in October 2023 [32]. Data collection for the anthropological component ended in January 2024, with the first results expected in September 2024.

### Phylogenetic Analysis

Phylogenetic data have been collected, with the first results expected by the end of 2024.

## Discussion

### Expected Findings

The expected results are described on the basis of findings from the literature. Given recent events in Haiti, most individuals are likely to have migrated within the past 10 years, driven primarily by insecurity and violence. Upon arrival in French Guiana, these individuals are expected to face significant economic hardship and social isolation, which may increase the likelihood of transactional sexual relationships and exposure to HIV, particularly among women.

In terms of mental health, the findings are anticipated to show a decline in well-being across all genders, with high rates of anxiety and depressive disorders and posttraumatic stress disorder. Moreover, people living with HIV are expected to be more vulnerable compared to HIV-negative individuals even though they are already facing considerable challenges.

Qualitative findings on health care access may suggest that migrants encounter numerous barriers to obtaining care in French Guiana, including administrative complexity, language and financial barriers, and mobility issues. In response to these challenges and the inadequacies of public services, support from NGOs and community organizations plays a crucial role in assisting migrants with social, health, and legal matters. Health mediators may further facilitate migrants’ access to care, supporting their social integration and empowering them in the process. On the other hand, the proximity between the prevention services delegated by the state to NGOs and newly arrived migrants facilitates early access to screening and prevention. The anthropological results are expected to emphasize the magical-religious perceptions surrounding health and HIV and the role of traditional medicine, including the use of plants in treatment and prevention. Phylogenetic analysis is likely to show a high prevalence of Caribbean B HIV subtypes and community clustering of transmission chains.

For a long time, it was difficult, particularly in France, to carry out surveys on people in relation to their native origin. In this work, after much reflection, the choice was made to work on people born in Haiti. Haiti’s history and very specific geographical situation suggest that Haitians arrive in French Guiana with their own particular baggage (eg, the natural and health disasters of 2010 and 2012). It is always difficult to work on a specific population according to its country of birth without running the risk of adding stigma to the discrimination already experienced by people living with HIV. However, since 2001, several studies have led the scientific community to consider the link between HIV and immigration from the perspective of inequalities [33,34]. A number of indicators point to the even greater difficulties faced by Haitians in French Guiana. Other elements reinforce the idea that Haitian-born people living in French Guiana are subject to particularly precarious situations, inequalities, and even discrimination, all of which are likely to have an impact on their health [35]. Again, keeping in mind the risk of oversimplification, the literature reminds us that health is mediated by social and political processes.

### Limitations

The study methodology has a number of limitations. First, the target population is hidden, most of them undocumented, and the situation (particularly in informal settlements) is rapidly changing. As information on their distribution was incomplete, it was difficult to assess the representativeness of this population in the territory in the absence of up-to-date comparative data. The recruitment sites were selected on a nonprobabilistic and reasoned basis, so selection bias cannot be excluded.

One of the limitations of this study is the strong stigma attached to the Haitian community, particularly the association between the terms “Haiti” and “HIV,” which has a historically negative connotation. This association could reinforce the stigma already attached to this population and limit acceptability.

The recruitment targets for the hepatitis B and HIV groups were ambitious, and the active referral files did not take into account patients lost to follow-up or the growing proportion of patients followed up on in the city (which is difficult to reach).

With regard to the inclusion of participants living with hepatitis B, the follow-up departments for these patients were late in signing up as this study group was added at a later stage, limiting the time available for recruitment.

### Strengths

The biographical approach is the first and principal strength of this work as the data illustrating life courses are embedded in time. This approach makes it possible to study the whole of a person’s life while placing events in the political and social context in which they took place. This approach also limits memory bias by grounding events in key life dates (eg, children’s births). This biographical approach was supplemented by a cross-sectional, qualitative, anthropological approach, and for people living with a chronic virus (HIV or hepatitis B), by a medical questionnaire. For people living specifically with HIV, a phylogenetic analysis was also proposed. All these sources make it possible to triangulate information and reinforce the internal validity of the results.

This is the first in-depth, mixed methodology study on Haitians living in French Guiana, shedding light on a significant population that is key in terms of public health. Despite the fact that the population is hidden and rapidly evolving, French Guiana is a small territory. Collaboration with the main actors in the field, with mediators from the community, and with an anthropologist specialized in French Guiana’s Creole communities increased the chances of obtaining a representative sample of the Haitian population living in French Guiana between 2021 and 2023.

Despite discussions on this point, targeting the Haitian population could be a source of discrimination, particularly when recruiting people living with HIV. In this study, the information and explanations provided by the mediator interviewers helped maximize understanding by building a relationship of trust with the participants, providing them with intelligible information, making them understand what was at stake, and limiting stigmatization. The mediators played a major role in promoting understanding, compliance with ethics, confidentiality, and respect for participants’ rights. The approach taken by community mediators played a major role in the project’s feasibility and the number of included participants. The Parcours d’Haïti mediator community network was undeniably a strength.

### Comparison With Prior Work

The ANRS Parcours 2012 to 2013 survey, a biographical study carried out in the Paris region among migrants from sub-Saharan Africa, was divided into 3 groups equivalent to those presented in this protocol (general population, people living with HBV, and people living with HIV). This study almost achieved its objectives with regard to the group of people living with HIV but fell short with regard to the group of people living with HBV and the general population [36]. This study revealed difficult living conditions on arrival and established the link between these living conditions and the acquisition of HIV in France [36]. The MAKASI study, carried out in 2019 as a follow-up to the ANRS Parcours 2012 to 2013 study among migrants from sub-Saharan Africa far from care, revealed low levels of health coverage and precarious administrative status, including among people who had been in the French territory for several years [37]. Previous surveys carried out in French Guiana show a very high level of food insecurity [38,39]. A number of studies have shown that the health of migrants in French Guiana and hexagonal France is deteriorating [4,40]. In terms of sexual health, recent studies highlight the high level of exposure to sexual violence among migrant women, the high level of transactional relationships used as a survival strategy, and the cumulative violence experienced by this population [4]. In light of recent literature studies published on the American continent, violence (physical and sexual) and the use of transactional sex are identified as one of the main components of the migratory trajectories for women in this area [41-44].

In the ANRS Parcours 2012 to 2013 survey, up to 50% of the people surveyed from sub-Saharan Africa contracted HIV after their arrival in France, and of these, 58% acquired HIV during the settlement period (between 0 and 6 years after migration), and 42% acquired HIV after settling (>6 years after migration) [45]. With regard to HIV, a number of studies have been carried out in French Guiana in recent years (including phylogenetic studies), enabling us to understand the factors driving the epidemic [9-11,14,16,17]. Elements similar to those found in the ANRS Parcours 2012 to 2013 study have been highlighted in these studies, with most foreigners living with HIV having acquired the virus after migrating to French Guiana [10,11]. The studies carried out showed that HIV was diagnosed later in Haitians than in native-born people but was detected more quickly in Haitians than in Surinamese individuals or Brazilians [17]. In light of the recent literature published on the American continent, numerous studies point to inconsistent condom use among migrant populations as well as a lack of knowledge about the risk factors and consequences of STIs [46-48].

### Assumptions and Hypothetical Study Outcomes

#### Quantitative and Biographical Data

In comparison with the results found in the literature, and particularly of the ANRS Parcours 2012 to 2013 study conducted in Paris area, we hypothesize that the study will reveal difficult living conditions after arrival in French Guiana and that these conditions will last for a long time. We will try to confirm that the departures from Haiti were precipitated by historical events and that the routes are more or less complex depending on the path taken. We hypothesize that migratory routes vary according to migration periods. We hypothesize that access to a residence permit is burdensome and that this is a factor negatively impacting the health of people arriving on the Guianese territory. We presume that access to formal housing is very limited and determined by the level of education and knowing someone in French Guiana previously. We hypothesize that relationships are determined by social conditions but that motherhood in women is more determined by age and social representations even when living conditions are precarious. We hypothesize that many people do not have the health coverage to which they are entitled and that health care services, although available, are not necessarily accessible (for reasons that include transport, health coverage, health literacy, and possible discrimination). We will also try to confirm the hypothesis that having contacts with NGOs and social services improves access to care compared to those who have not benefited from this support. We also make the assumptions that people from Haiti experience high levels of food insecurity after arriving in French Guiana and that many people are isolated.

We also hypothesize that the mental health of Haitians living in French Guiana is impaired when living conditions are precarious, violence has occurred, or relatives are separated.

During these years, people may be exposed to situations of sexual vulnerability and to unwanted sexuality and transactional, paid, or even forced sex, exposing them to a greater risk of acquisition of HIV or STIs and psychological trauma. In terms of sexual health, we hypothesize that, regardless of the participant group, a large proportion of the population has been exposed to sexual violence and transactional relationships and that these phenomena particularly concern women. Finally, we hypothesize that the use of contraception is low and that recourse to abortion is very limited.

Concerning the follow-up of people living with HIV and people living with HBV, we hypothesize that Haitian populations in French Guiana use screening relatively early and that those diagnosed with HIV enter care relatively early, in line with the screening and mediation services available in the region, notably through the French Red Cross. We also think that impaired social conditions, social isolation, and low health literacy are associated with a delay in screening. A catch-up certainly exists for women during pregnancy. It is likely that periods of disruption of care are closely linked to the social situation of the people concerned, which changes from year to year. The biographical approach will enable us to confirm the hypothesis that, in the years during which a disruption in care occurred, the person faced social or administrative difficulties more often. In addition, we assume that periods of loss to follow-up are more frequent among people living with HBV, linked to an incomplete understanding of the disease, the absence of therapeutic indications for a large proportion of people living with HBV, prolonged follow-up intervals, and a lower civil society investment than that in people living with HIV. With regard to people living with HIV, we hypothesize that they will report unprotected sex in the years following their infection.

Finally, we hypothesize that conducting a long interview focusing on health issues is likely to contribute to respondents’ access to and use of health care.

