### Study Populations and Inclusion Criteria

For the quantitative epidemiological and biographical component, participants were included in 3 groups: a general population group, a group of people living with HIV, and a group of people living with HBV.

The inclusion criteria for all groups were as follows: being born in Haiti (regardless of current nationality), having been in French Guiana for >3 months, being aged between 18 and 60 years, and having no objection to participate in the study. For the group of people living with HIV, the inclusion criteria were as follows: living with HIV and having a diagnosis dating back >3 months (whatever their status with regard to hepatitis B and C), as well as being followed up on by one of the study’s partner physicians at the hospitals in Cayenne, Kourou, or Saint-Laurent-du-Maroni; in outpatient care; or by a partner association. For the group of people living with chronic hepatitis B, the inclusion criteria were living with a chronic HBV infection and having been diagnosed for >3 months (not coinfected with HIV), as well as being followed up on by one of the study’s partner physicians in the hospitals of Cayenne, Kourou, or Saint-Laurent-du-Maroni; in outpatient care; or by a partner NGO.

For the general Haitian population group (not known to live with HIV or HBV), the inclusion criteria were declaring that they were not infected with either HIV or HBV, being under the care of one of the study’s partner physicians, or being recruited in the public space of one of the cities targeted by the study (Cayenne, Matoury, Rémire-Montjoly, Macouria, Kourou, Montsinéry-Tonnegrande, Sinnamary, Maripasoula, Saint-Laurent-du-Maroni, or Mana). Exclusion criteria were being unable to answer the interviewer in French or Haitian Creole; being under guardianship, tutelage, or legal protection; and having already answered the study questionnaire.

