### Participant Enrollment, Sampling Approaches, and Monitoring

For the quantitative aspects of the study, sampling of the Haitian population in French Guiana—little explored, partially hidden (living in informal settlements and without papers), and rapidly evolving—was carried out by combining several methods. Recruitment sites were chosen on a nonprobabilistic and reasoned basis. Locations were selected based on literature analysis, census data, knowledge of the peer community workers, knowledge of partner NGOs, and accessibility and safety. These criteria are listed in Figure 1. Finally, partner hospital departments, outpatient centers (health care access offices, French Red Cross prevention and health centers, and primary care centers), and general practitioners were identified. The hospital services selected were those that limited bias on morbidity (particularly chronic diseases). The medical departments selected for participant screening and enrollment were maternity, pediatrics, dermatology, and the emergency room. In view of the enrollment sites mentioned, an oversampling of women was expected and judged as acceptable.

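### Maternity recruitment selects women on a birth around the interview, so the living-conditions odds ratio for motherhood is biased whenever maternity recruits differ socially from other women; the direction is not known

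*Protocol article*

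**What the plan says.** On recruitment, the section on enrollment and sampling states: "The medical departments selected for participant screening and enrollment were maternity, pediatrics, dermatology, and the emergency room". These services were chosen to limit bias related to morbidity. The only other consequence weighed is the sex balance: "an oversampling of women was expected and judged as acceptable". Site choice as a whole was purposive: "Recruitment sites were chosen on a nonprobabilistic and reasoned basis". The general population group could also be reached by "being under the care of one of the study’s partner physicians, or being recruited in the public space of one of the cities" on a list in the inclusion criteria, and snowball cards were planned in addition.

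On data, the section on collection tools says that the biographical grid records pregnancies, children and screening tests year by year.

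On analysis: "Factors associated with biographical key indicators will be analyzed year after year using discrete-time logistic regression models that take into account time".

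On hypotheses, the section on assumptions and hypothetical outcomes expects that "motherhood in women is more determined by age and social representations even when living conditions are precarious". On screening it says: "A catch-up certainly exists for women during pregnancy". The Conclusions section says that the analyses will test the study's hypotheses. The Limitations section admits possible selection bias from site choice in general terms and does not connect it with pregnancy or motherhood.

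**The concern.** A woman enrolled as a patient in maternity has a pregnancy or birth in or near the interview year because that is how she was found. For her, the outcome of a yearly birth model does not vary in that year. The sample therefore joins women selected on the outcome to women met by other routes, and the article weighs only morbidity and sex balance in accepting this.

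Two stated expectations are exposed: that living conditions matter less than age and social representations for motherhood, and that screening catches up in pregnancy. If the social mix differs between maternity and the other sites, the living-conditions coefficient partly reflects where women were met. A result for or against the motherhood hypothesis could then come from recruitment.

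**Working it through.** The article gives no figure for the motherhood or screening models. Its one sample-size figure reproduces (1.96² × 0.25 / 0.05² = 384.16, stated as 384) and does not bear on this point. All inputs below are assumptions.

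**Inputs for the interview year.** Share precarious 0.6; annual birth risk 0.08 in non-precarious women; true odds ratio 1.5. The odds are then 0.08/0.92 = 0.0870 and 1.5 × 0.0870 = 0.1304, so the risk in precarious women is 0.1304/1.1304 = 0.1154. The overall risk is 0.6 × 0.1154 + 0.4 × 0.08 = 0.0692 + 0.0320 = 0.1012. Let f be the share of women recruited in maternity.

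**1. Level.** Interview-year birth proportion = f + (1 − f) × 0.1012. For f = 10%, 25% and 50% this is 0.191, 0.326 and 0.551, against 0.101 without maternity recruitment.

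**2. Selection on the birth alone (f = 25%).** Maternity recruits have the precarious share of all births, 0.0692/0.1012 = 0.684.
- Births: precarious 0.25 × 0.684 + 0.75 × 0.0692 = 0.2229; other 0.25 × 0.316 + 0.75 × 0.0320 = 0.1030.
- Ratio of precarious to other among women without a birth: (0.6 × 0.8846)/(0.4 × 0.92) = 1.442.
- Odds ratio (0.2229/0.1030)/1.442 = 1.50: no bias.

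**3. Other sites lean 2:1 to precarious women.** Their precarious share becomes 1.2/1.6 = 0.75.
- Births: 0.1710 + 0.75 × 0.75 × 0.1154 = 0.2359, and 0.0790 + 0.75 × 0.25 × 0.08 = 0.0940.
- Without a birth: (0.75 × 0.8846)/(0.25 × 0.92) = 2.885.
- Odds ratio (0.2359/0.0940)/2.885 = 0.87: biased down.

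**4. Maternity sites lean 2:1 instead.** The precarious share of maternity recruits is 1.368/(1.368 + 0.316) = 0.812.
- Births: 0.2031 + 0.0519 = 0.2550, and 0.0469 + 0.0240 = 0.0709.
- Odds ratio (0.2550/0.0709)/1.442 = 2.49: biased up.

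**5. Both lean 2:1.** Births: 0.2031 + 0.0649 = 0.2680, and 0.0469 + 0.0150 = 0.0619. Odds ratio (0.2680/0.0619)/2.885 = 1.50: no bias.

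**6. All post-arrival years.** Earlier years dilute the effect. The simulation assumed about 10% annual births, six years, half of women precarious and 10–20% of women from maternity; the true odds ratio is 1.5.

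| Recruitment | Fitted, all years |
|---|---|
| Depends on the birth only | 1.48–1.51 |
| Other sites lean 2–3:1 to precarious women | 1.35–1.17 |
| Maternity sites lean 2:1 to precarious women | 1.61–1.69 |
| Either lean, maternity recruits' person-years ended before the index birth | 1.48–1.52 |
| Same truncation, fecundity varying between women | 1.33–1.56 |

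A second simulation, adjusted for age and years since arrival, with maternity shares of 10/25/50% and a 2:1 lean, gave 1.45/1.38/1.39 (other sites lean) and 1.65/1.78/1.96 (maternity leans).

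**7. Pediatrics.** A child seen there may be years old, so what is conditioned on is being a mother, not a birth in the interview year. Recruiting women with any birth since arrival gave 1.46–1.48 for a true 1.5, a small attenuation at most.

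**8. Screening catch-up.** True odds ratio 4 for pregnancy and 0.6 for precariousness, maternity shares up to 50%. If maternity recruits are a random sample of pregnant women, the fitted pregnancy odds ratio is 3.95–4.04. If only women already screened are met there, it is 4.8, 6.1 and 7.8 at shares of 10%, 25% and 50%. The precariousness odds ratio stays at 0.60–0.62 in both cases.

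**The case against.** The strongest reply is that sampling on the outcome does not bias a logistic odds ratio. That is correct (steps 2 and 5), and it rules out a reading a reader might infer: that maternity recruitment as such pulls the effect of precariousness down and so favors the study's own hypothesis. A downward bias needs the other sites to lean more to precarious women than maternity does, and no section establishes this. The other routes include dermatology, the emergency room, general practitioners, public space and snowball cards, the last intended to reduce selection on care, support and insecurity. The opposite lean is equally compatible with the text.

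Second, the article does not name motherhood as one of the yearly indicators to be modelled. The link is an inference from the hypothesis, the yearly pregnancy data and the stated intention to test the hypotheses. It is a reasonable inference, but it is one.

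Third, site choice is already listed as a limitation, and adjustment for recruitment site could sit in a full analysis plan that is not shown. That stands as a caution. It does not remove the point, because the article itself gives the reasons for accepting these departments, and selection on pregnancy is not among them.

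A reader might also infer that age must come out as the stronger factor because the grid starts at birth. The article does not state the risk period of the model, so this does not follow.

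**Conclusion.** The concern holds in a conditional form. Interview-year birth levels are inflated by maternity recruitment. The living-conditions odds ratio in yearly birth models is biased if maternity recruits and other women differ in social mix: downward if the other sites lean to precarious women, upward if the maternity sites do, and not at all if they lean equally. With 10–20% of women from maternity and leans of 2–3:1 (other sites) or 2:1 (maternity), a true 1.5 becomes 1.35–1.17 or 1.61–1.69 over all years. The documents give neither the share nor the lean, so these figures show possible size and are not an estimate for this study.

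The pregnancy catch-up is overstated only under the further assumption that women already screened are preferentially met in maternity. Pediatrics raises a weaker, different issue. The results rest on births being independent across years given precariousness; relaxing this leaves some residual bias after the fix.

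**What to change.** In models of pregnancy, birth and pregnancy-linked screening, end the person-years of women recruited in maternity before the index pregnancy. As a sensitivity analysis, repeat these models without women recruited in maternity or pediatrics. Judge the motherhood hypothesis on the living-conditions coefficient and its confidence interval; a stronger coefficient for age does not test living conditions.

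The cost is a few lines of analysis wording and a filter on recruitment site, and the article says that analyses had not begun at submission. The filter needs recruitment site to be on file, which the article does not state. Some person-years and the index pregnancies are lost, and a small bias can remain if fecundity varies between women (1.33–1.56 for a true 1.5 in the simulation).
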